### Power calculation

An a priori power analysis was performed to calculate the minimum of needed study participants to conduct a SEM analysis. We assumed a power (1-β) of 0.90 with an effect size of 0.15 and an alpha of 0.05. With these settings a sample size of at least 870 was required to achieve a robust model with 5 latent variables. With estimated screening failures of slightly less than 10% (e.g. development of bipolar disorder in the further course, or with inclusion concealment of a dependence illness) we aim to recruit 950 participants at inclusion. We aim to recruit a sample size of 475 patients with depression and 475 participants without depression. Recruitment in the project presented here will end when the sample size of 950 subjects is reached. Also, this is a sufficient number of participants for machine learning algorithms [106].

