## Abstract

Unipolar depression is a prevalent and disabling condition, often left untreated. In the outpatient setting, general practitioners fail to recognize depression in about 50% of cases mainly due to somatic comorbidities. Given the significant economic, social, and interpersonal impact of depression and its increasing prevalence, there is a need to improve its diagnosis and treatment in outpatient care. Various efforts have been made to isolate individual biological markers for depression to streamline diagnostic and therapeutic approaches. However, the intricate and dynamic interplay between neuroinflammation, metabolic abnormalities, and relevant neurobiological correlates of depression is not yet fully understood. To address this issue, we propose a naturalistic prospective study involving outpatients with unipolar depression, individuals without depression or comorbidities, and healthy controls. In addition to clinical assessments, cardiovascular parameters, metabolic factors, and inflammatory parameters are collected. For analysis we will use conventional statistics as well as machine learning algorithms. We aim to detect relevant participant subgroups by data-driven cluster algorithms and their impact on the subjects’ long-term prognosis. The POKAL-PSY study is a subproject of the research network POKAL (Predictors and Clinical Outcomes in Depressive Disorders; GRK 2621).

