### Medical examinations

#### Clinical assessments

Depressive symptomatology is assessed using self-rated instruments (PHQ-9), the Inventory of Depressive Symptomatology (IDS-SR) [73] and observer ratings (MADRS) at inclusion and each follow-up [74]. At inclusion functionality will be rated using the General Assessment of Functioning (GAF) [75, 76]. To precisely detect possible exclusion criteria a SCID-5-CV rating is performed at study inclusion. All assessments are done by experienced and trained raters [77]. Furthermore, a rating is conducted where the raters need to describe their own impression concerning prognosis and give an estimate concerning the disease trajectory.

The abdominal circumference, as well as the hip circumference are measured standing with the upper body free with a measuring tape according to the guidelines of the WHO [78]. Blood pressure measurement (systolic, diastolic) and pulse is performed after 3–5 min of rest while sitting [79]. In addition, body temperature is determined with a tympanic thermometer in the morning [80].

Heart rate and HRV are measured using special chest straps (EcgMove4) from Movisens (Movisens GmbH), which determines body position. A HRV measurement is performed at each follow-up. The participants are kindly asked to be in an upright position for 5 min and lie for 5 min while breathing at a normal pace to achieve a resting state measurement [81]. If needed, participants can take breaks. Each participant should wear the belt at least for 10 min. Healthy controls will wear the belt for 24 h5 if possible. Blood is drawn between 8:00–10:00 in the mornings and analyzed at the Institute of Laboratory Medicine (LMU Hospital). Specifically, glucose, liver values, cholesterol (HDL and LDL), triglycerides, cortisol, TSH, AAT-1, IGF-1, CRP, and complete blood count are measured. The participants are asked not to smoke and to conduct an overnight fast before the examination. If participants are additionally willing to take part in the Munich Mental Health Biobank Project (MMBH), [82] further blood is drawn (9 ml Serum, 9 ml Li-Heparin, 7.5 ml EDTA, 2.4 ml RNA Extract) and stored at – 80 °C. Further analysis of MMHB blood samples is possible in following projects.

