### Planned data analyses

Categorical data will be one-hot-encoded if suitable and summarized with percentages and confidence intervals. For ordinal data the median will be given as well as the interquartile range and for continuous data we calculate the mean as well as the standard deviation and the confidence intervals. Demographic and baseline characteristics in the study arms will be compared with suitable statistical tests. Since multiple comparisons will be performed significant *p*.values will be reported false discovery rate corrected [107]. With the cross-sectional data at inclusion a SEM analysis will be conducted [108]. Furthermore, we will investigate the predictive value of baseline biological parameters for change in depressive symptomatology. In addition, we will design a classification algorithm using all relevant data detecting which participant is depressed. This approach involves the implementation of multiple supervised machine learning algorithms to thoroughly assess their performance. We will evaluate each algorithm during the analysis stage and subsequently select the one that yields the most favorable results. These algorithms may include, but are not limited to, support vector machines, decision trees, and neural networks. Each of these algorithms will be carefully applied and evaluated in the context of our research question. Furthermore, we will use multimodal stacked algorithms to assess the generalizability of different clinical questionnaires and biomarkers separately. To ensure the robustness of our algorithm selection and model performance assessment, we will employ a leave-site-out nested cross-validation approach in each model. This mitigates the risk of overfitting and ensures generalizability. Since the eventual goal of our algorithm is the implementation in a clinical context and to guide general practitioners, we plan to develop a sequential prediction model, which reduces the number of required data modalities and diagnostic uncertainty, as described by Koutsouleris et al. [109]. Sequential stacking models can be used to reduce the data required to produce optimum prediction scores. This method can greatly increase clinical applicability since physicians will be only asked for additional information if needed to achieve satisfactory predictive accuracy [109].

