### Strengths and limitations of this study

The presented study has particular value since especially in Germany, outpatient samples are rare. Even more so if they are longitudinal and prospective. As a result, the comprehensive outcome measures will provide unique information about physical and emotional health of the participants. Commonalities and differences in transition pathways and outcomes will contribute to identifying groups of patients who might benefit from differing treatment approaches or who might need more intensive care early on to improve the long-term outcome. Since a prospective period of 5 years is long and the medical examinations are only annually there might be high dropout rates, because participants might move to other places or might feel less willing to participate in our study, potentially leading to an attrition bias [130]. Since healthy participants will also be recruited by flyers, especially trained and weight conscious participants might be attracted to the study because of the usage of the bioimpedance scale, potentially leading to a sampling bias.

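### Leave-site-out validation in a sample enriched to about 50% depressed cannot show that predicted probabilities and predictive values hold at GP prevalence, and longer HRV recording in healthy controls could confound the models

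*Protocol article*

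**What the plan says.** The Power calculation section sets the balance of the sample: "We aim to recruit a sample size of 475 patients with depression and 475 participants without depression". Methods and design divides the second half into 425 participants without depression and 50 healthy controls. It plans to recruit 90% of the cohort in GP offices, with others from a university psychiatric outpatient clinic. The limitations section adds a further route: "Since healthy participants will also be recruited by flyers".

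Planned data analyses introduces a classifier that detects who is depressed, and a sequential model that asks physicians for more data only when needed. The purpose is explicit: "Since the eventual goal of our algorithm is the implementation in a clinical context and to guide general practitioners". The same section says that leave-site-out nested cross-validation guards against overfitting and secures generalizability. Secondary outcomes adds a test of the cross-sectional algorithm on follow-up data for the same reason.

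On HRV, Clinical assessments states "Each participant should wear the belt at least for" 10 minutes, and Table 2 sets 5 minutes in each of two positions. It also states "Healthy controls will wear the belt for 24" hours where possible.

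The non-depressed cohort is described in three ways. The Abstract has "individuals without depression or comorbidities, and healthy controls". Study aims and hypotheses has primary care patients free of psychiatric disorders. Methods and design has participants without depression and stresses that patients with somatic comorbidity are included.

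**The concern.** Leave-site-out validation tests whether a model transfers between sites of the kind sampled. It cannot test transfer to a population with a different share of cases when the whole sample is enriched. Follow-up visits of the same participants do not supply that population either. PPV, NPV and predicted probabilities all depend on the share of cases, and a physician acts on these quantities. If the sequential model decides from predicted probabilities when to ask for more data, cut-offs tuned at 50% would be misplaced in practice.

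Two features of the comparator add to this. Healthy controls are likely to be easier to separate from cases than somatically ill GP patients are. In addition, their HRV recordings may be much longer than anyone else's, although Primary outcome expects HRV, with IGF-1 and AAT-1, to be a main driver of prediction.

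**Working it through.** **The plan's own figures.** The article states "We assumed a power (1-β) of 0.90 with an effect size of 0.15 and an alpha of 0.05" and "With these settings a sample size of at least 870 was required to achieve a robust model with 5 latent variables". It does not name the formula. Of several variants tried, one gives exactly 870: the normal-approximation lower bound for detecting an effect of 0.15 in a structural equation model, two-sided, power 0.90, with alpha Šidák-adjusted over the 10 pairs of 5 latent variables, 1 − 0.95^(1/10) = 0.0051. Allowing for failures, 870/(1 − 0.084) = 950, which fits slightly less than 10%. The cohorts add up: 50 + 475 + 425 = 950 and 50 + 425 = 475. These figures are not in dispute. They size the structural equation model and do not bear on prevalence.

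**Inputs for the check.** Sample prevalence is 475/950 = 0.50. The Introduction gives 15.4% and 9.8% (worldwide point prevalence in two periods) and 4.6% (12-month prevalence). Sensitivity (Se) and specificity (Sp) are not stated, so 0.80 is an assumption, with a range of 0.70 to 0.90.

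**Predictive values and probabilities**, with p the prevalence:

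- PPV = p·Se / [p·Se + (1 − p)(1 − Sp)]
- NPV = (1 − p)·Sp / [(1 − p)·Sp + p(1 − Se)]
- Corrected odds = predicted odds × p/(1 − p), because the sample odds are 1. The logit offset is ln[p/(1 − p)].

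Example at 15.4%: PPV = 0.1232/(0.1232 + 0.1692) = 0.42.

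| Prevalence | PPV, Se = Sp = 0.70 | PPV, 0.80 | PPV, 0.90 | NPV, 0.80 | Predicted 0.50 becomes | Logit offset |
|---|---|---|---|---|---|---|
| 50% | 0.70 | 0.80 | 0.90 | 0.80 | 0.50 | 0 |
| 15.4% | 0.30 | 0.42 | 0.62 | 0.96 | 0.154 | −1.70 |
| 9.8% | 0.20 | 0.30 | 0.49 | 0.97 | 0.098 | −2.22 |
| 4.6% | 0.10 | 0.16 | 0.30 | 0.99 | 0.046 | −3.03 |

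If GP prevalence were 25% (an assumption), PPV at 0.80/0.80 would be 0.20/(0.20 + 0.15) = 0.57.

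**Healthy controls.** Their share of non-cases is 50/475 = 10.5%. With assumed specificity of 0.70 in GP patients and 0.90 in healthy controls, the pooled value is (425 × 0.70 + 50 × 0.90)/475 = 0.721, a gain of 2.1 points. Over assumed pairs from 0.70/0.80 to 0.70/1.00, the gain is 1.1 to 3.2 points.

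**HRV.** Suppose longer recording shifted an HRV feature by 0.5 SD (an assumption) in all 50 healthy controls. The mean of the whole non-depressed group would then move by 0.105 × 0.5 = 0.05 SD. In a direct contrast with healthy controls, which the first hypothesis includes, the full 0.5 SD would appear.

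**Comparator wording.** A cohort without comorbidities (Abstract) and one that includes somatic comorbidity (Methods and design) cannot be the same. This affects 425 of the 475 non-cases, or 89%.

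**The case against.** A reader might infer that the article presents accuracy in this sample as performance in general practice. It does not. No predictive value is stated or promised, GP use is called an eventual goal, 90% of participants are to come from GP offices, and the Discussion says that validation in a follow-up study would be necessary. Enriching for cases is a legitimate choice when developing a model, and a condensed article need not describe recalibration.

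A reader might also infer that accuracy as a whole is invalid. Sensitivity and specificity do not change with prevalence alone, the healthy controls move pooled specificity little, and the article itself discloses the sampling bias from flyers. PPV does not apply to the primary outcome, which is prediction of severity. The article does not say that the sequential model uses probability cut-offs.

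Finally, a reader might infer that HRV effects will not hold. Everyone has the same 5 + 5 minute recording, and no section says that 24-hour data replace it.

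All of this stands and narrows the point. What remains does not depend on omitted detail: the article names a safeguard and credits it with more than it can deliver. Later validation would not repair cut-offs already set at 50% prevalence.

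**Conclusion.** The point holds in limited form. The generalizability statement is too strong, because neither held-out sites nor follow-up visits leave the enriched sample. At an assumed sensitivity and specificity of 0.80, PPV falls from 0.80 to between 0.16 and 0.42. Over 0.70 to 0.90, it lies between 0.10 and 0.62 at the article's prevalences. These prevalences are stand-ins for GP attenders; a higher true value would shrink the gap. NPV moves the other way, from 0.80 to 0.96–0.99. The probability shift assumes that marker distributions among cases and among non-cases are the same in the sample as in practice.

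The healthy-control effect on specificity is small. The HRV concern is conditional on 24-hour data entering the models. The contradictory descriptions of the non-depressed cohort matter because specificity depends on which one applies. This is an inexpensive improvement that should be made, not a flaw that undermines the study.

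**What to change.** - State a GP prevalence range, and recalibrate predicted probabilities to it before setting sequential cut-offs or reporting PPV and NPV. For a logistic model this is an intercept shift.
- Report diagnostic performance primarily in GP-recruited participants, with healthy controls and clinic patients shown separately.
- Reconcile the three descriptions of the non-depressed cohort.
- Derive the HRV features used in models from the common 5 + 5 minute segments in every cohort, and use 24-hour recordings descriptively.
- Limit the generalizability statement to transfer across sites with the same case mix.

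No new data are needed. The cost is plan wording, one recalibration step, about 10% fewer participants in the headline accuracy estimate (0.10 × 950 = 95) and a less favourable PPV.

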### Planned data analyses

Categorical data will be one-hot-encoded if suitable and summarized with percentages and confidence intervals. For ordinal data the median will be given as well as the interquartile range and for continuous data we calculate the mean as well as the standard deviation and the confidence intervals. Demographic and baseline characteristics in the study arms will be compared with suitable statistical tests. Since multiple comparisons will be performed significant *p*.values will be reported false discovery rate corrected [107]. With the cross-sectional data at inclusion a SEM analysis will be conducted [108]. Furthermore, we will investigate the predictive value of baseline biological parameters for change in depressive symptomatology. In addition, we will design a classification algorithm using all relevant data detecting which participant is depressed. This approach involves the implementation of multiple supervised machine learning algorithms to thoroughly assess their performance. We will evaluate each algorithm during the analysis stage and subsequently select the one that yields the most favorable results. These algorithms may include, but are not limited to, support vector machines, decision trees, and neural networks. Each of these algorithms will be carefully applied and evaluated in the context of our research question. Furthermore, we will use multimodal stacked algorithms to assess the generalizability of different clinical questionnaires and biomarkers separately. To ensure the robustness of our algorithm selection and model performance assessment, we will employ a leave-site-out nested cross-validation approach in each model. This mitigates the risk of overfitting and ensures generalizability. Since the eventual goal of our algorithm is the implementation in a clinical context and to guide general practitioners, we plan to develop a sequential prediction model, which reduces the number of required data modalities and diagnostic uncertainty, as described by Koutsouleris et al. [109]. Sequential stacking models can be used to reduce the data required to produce optimum prediction scores. This method can greatly increase clinical applicability since physicians will be only asked for additional information if needed to achieve satisfactory predictive accuracy [109].

Further, we recognize the necessity of employing cluster analysis techniques to gain insights into the heterogeneous nature of depression [17]. It is likely that depression does not encompass a single biological phenotype but rather multiple distinct profiles. To comprehensively address this, we will utilize various clustering algorithms. Our primary clustering algorithm will be non-negative matrix factorization [110]. Subsequently, we will select the clustering algorithm that best aligns with the clinical realities reflected within the identified clusters.

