## Methods and design

The POKAL-PSY study is a prospective study with three cohorts, where we recruit one cohort with healthy controls (*n* = 50), patients with depression (*n* = 475) and participants without depression (*n* = 425) where participants are monitored for five years. Notably, our emphasis on recruiting individuals with and without depressive symptoms serves to comprehensively investigate the predictors and underlying mechanisms of unipolar depression. The inclusion of patients with somatic comorbidities, who frequently seek medical care, highlights a real-world scenario. For this project, participants will be recruited in a naturalistic setting. Cardiovascular factors (heart rate variability, pulse, blood pressure), metabolic factors (blood lipids, HbA1c, body fat percentage, fasting glucose, IGF-1), as well as inflammatory markers (CRP, AAT-1) will be collected. In addition, the burden of somatic symptoms, lifestyle factors (Eating behavior, chronotype, physical activity), psychopathological characteristics (depression subtype, childhood trauma, anxiety) will be assessed by questionnaires. Depressive relapses will be assessed anamnestically if they occur during the follow-up visits. Patients will be mainly recruited in general practitioner (GP) offices, affiliated with the Bavarian Research Practice Network. Currently, we are recruiting at three different sites. By the end of the recruiting process, our goal is to have recruited from 5 to 6 different sites. We plan to recruit 90% of our study cohort within several GP offices. The inclusion and exclusion criteria are checked in consultation with the treating GPs and in direct patient contact by the study staff and the patients' written consent is obtained. In addition, participants will be recruited at the psychiatric outpatient clinic of the university clinic in Munich. In the context of the POKAL project we cooperate with other research groups and projects by providing validation datasets and support concerning participant recruitment. Specifically, we will cooperate with the MIP3 project (project nr. 21–0357, German Clinical Trials Register number: DRKS00025946). The healthy controls recruited will consist of motivated German citizens. All study personnel were trained to conduct the HRV measurements, as well as the observer ratings. Organizational project management is performed by the Studienzentrum Psychiatrie (SZP) of the LMU Munich. All participants sign a written informed consent form prior to participation. The study was approved by the local ethics committee (project nr. 22–0637, date 14.09.2022) and registered at ClinicalTrials.gov (NCT05547711) and at the German Clinical Trials Register (DRKS00030203). The study presented here is a subproject of the research network POKAL (Predictors and Clinical Outcomes in Depressive Disorders; GRK 2621), which is sponsored by the German Research Foundation (DFG) [70]. Furthermore, all the participants are kindly asked whether they give written consent to participate in the Munich Mental Health Biobank, as well [71]. The POKAL-PSY study is performed in accordance with the regulations of good clinical practice and the declaration of Helsinki [72]. The eligibility criteria can be seen in Table 1.

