#### Mediating variables

Lifestyle factors, personality traits, and personal history are considered to be mediating variables. We will consider blood pressure, medication, age, and gender as confounding factors. The breathing rate is not monitored [105].

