### Development of an algorithm to detect unipolar depression

The study presented here can be used to establish an algorithm that is supposed to facilitate the diagnosis of unipolar depression in an outpatient setting. Such a tool would be particularly valuable because most studies of unipolar depression are conducted primarily in the hospital setting. Currently, only about half of depressed patients in an outpatient setting are detected, where again only a fraction receives treatment [10]. Current screening rates for unipolar depression in primary care are low, despite the high socioeconomic burden, emphasizing the dire need of fast and easy to use algorithms [124]. In a further step, validation of the model by a follow-up study would be necessary [125]. Prognosis of affected people worsens if their symptomatology goes undetected for a long time [126]. Regarding the high lifetime prevalence as well as the probability of a relapse, routine screening data indicate that a routine screening for unipolar depression is cost-effective [127]. Several barriers were identified in a qualitative study. First, primary care physicians could not adequately perform the screenings due to a lack of time, and second, there was a lack of capacity to provide patients with the ideal treatment. Third, it was also observed that, due to stigmatization, patients were only honest about their symptoms if they had established the necessary basis of trust with their family doctor [124]. Having said this, the algorithm could help primary care physicians to overcome those boundaries more easily. In 2021 Fusar-Poli et al. described the potential of preventive psychiatry to profoundly improve mental health services in our society, since currently mental health services are not focussing on the prevention of unipolar depression or other mental disorders. A “one-size fits all” approach is, according to Fusar-Poli, not effective; he stresses the need for precision psychiatry together with preventive measures in a primary care setting. Often patients at risk show rather nonspecific symptoms impeding early detection in a primary care setting [128]. Through effective stratification, precision psychiatry will significantly improve medical care for individuals [129].

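### The diagnostic classifier is meant to help GPs who miss depression, but its cases may already be diagnosed or treated, and the plan neither bars history and medication as inputs nor isolates unrecognised cases

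*Protocol article*

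**What the plan says.** **Purpose.** The Abstract and Introduction present depression that GPs fail to recognise as the problem (about 50% missed; 55% detected). The Discussion repeats it: "Currently, only about half of depressed patients in an outpatient setting are detected, where again only a fraction receives treatment". Planned data analyses gives guidance of GPs as the eventual goal.

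**Cases.** The only depression-specific inclusion criterion in Table 1 is PHQ > 8. No inclusion or exclusion criterion concerns prior diagnosis of depression or current treatment. Ninety per cent of the cohort is to come from GP offices. Methods and design then adds: "In addition, participants will be recruited at the psychiatric outpatient clinic of the university clinic in Munich". The Power calculation gives the group sizes: "We aim to recruit a sample size of 475 patients with depression and 475 participants without depression".

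**Comparators.** Study aims and hypotheses defines them as primary care patients without psychiatric disorders and healthy controls with no prior medical history.

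**Inputs.** For the diagnostic model, "we will design a classification algorithm using all relevant data detecting which participant is depressed". Table 2 lists medical history in the inclusion questionnaire, and the Self-rating questionnaires section says this covers psychiatric disorders. The primary outcome is a different model. It predicts severity from routine blood markers and HRV, with single self-rating items only where needed.

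**Safeguards.** Under Mediating variables: "We will consider blood pressure, medication, age, and gender as confounding factors". Validation is leave-site-out nested cross-validation. The article describes no performance estimate by recognition or treatment status.

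**The concern.** The patient for whom a GP needs help is one whose depression has not been recognised. A classifier trained on a mixture of recognised and unrecognised cases can succeed for reasons that do not carry over to that patient. There are two routes.

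1. *Label leakage.* If prior psychiatric diagnosis or psychotropic medication is an input, the model reads off a diagnosis that someone has already made. The comparator definition sharpens this, because people without psychiatric disorders will rarely carry such an entry.
2. *Treatment effects.* Even with those items left out, effects of treatment on weight, metabolic markers and HRV could separate treated cases from untreated comparators.

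The plan also keeps whichever algorithm performs best. Judged on pooled performance, that rule favours models that exploit either route. At stake is whether the reported accuracy says anything about finding missed depression.

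**Working it through.** **1. The plan's own figures.** The Power calculation takes alpha 0.05, power 0.90 and effect size 0.15, and concludes: "With these settings a sample size of at least 870 was required to achieve a robust model with 5 latent variables". I used the a priori lower bound for SEM sample size, with a two-sided alpha Šidák-corrected over the 5×4/2 = 10 pairs of latent variables. The correlation term ρ = 0.15 is my assumption, since the article does not give one.

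- Corrected alpha: 1 − 0.95^(1/10) = 0.00512. The z-values sum to 2.800 + 1.282 = 4.081.
- H = (0.15/4.081)² = 0.001351
- A = 1 − ρ² = 0.9775; B = ρ·arcsin(ρ/2) = 0.01126; C = ρ·arcsin(ρ) = 0.02259; D = A/√(3 − A) = 0.6873
- t = A(π/6 − B + D) + H = 1.1740
- n = [t + √(t² + 4AH(π/6 + √A + 2B − C − 2D))]/(2H) = 869.2, rounded up to 870. With ρ = 0 it is 912.

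For losses, "With estimated screening failures of slightly less than 10" per cent: 1 − 870/950 = 8.4%, which fits. These figures are sound on their own inputs, but they size the SEM only. They guarantee no number of unrecognised cases.

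**2. How many cases could come from the clinic.** Outside GP offices: 10% × 950 = 95 participants. If every one were a depressed clinic patient, that is 95/475 = 20% of cases. This is a ceiling. No clinic quota is given, and healthy controls may also come from outside GP offices. Recognised cases seen in GP offices come on top and cannot be counted.

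**3. How many cases could be unrecognised (share assumed).**

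| Unrecognised share | Cases of 475 |
|---|---|
| 0% | 0 |
| 10% | 48 |
| 25% | 119 |
| 45% (mirrors the Introduction's 55% detected) | 214 |
| 60% | 285 |

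**4. What a marker of recognition or treatment would do.** Take a yes/no marker present in a share t of cases and c of non-cases, carrying no other information about depression. Its AUC is 0.5 + (t − c)/2. Assume c = 5%:

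| t | Pooled AUC |
|---|---|
| 20% | 0.575 |
| 40% | 0.675 |
| 60% | 0.775 |
| 80% | 0.875 |

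Among unmarked cases t = 0, so the AUC is 0.5 − 0.05/2 = 0.475 in every row. A respectable pooled figure can therefore coexist with no ability to find the unrecognised patient.

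**5. Effect on sensitivity.** With a recognised share s, pooled sensitivity exceeds that in unrecognised cases by s × (sensitivity in recognised − sensitivity in unrecognised). With assumed sensitivities of 85% and 60%, the excess is 0.4 × 25 = 10 points at s = 40%, 15 points at s = 60% (pooled 75%) and 22.5 points at s = 90%. If the two sensitivities are equal, the excess is zero.

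Steps 3 to 5 show the mechanism. They do not estimate the bias in this study.

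**The case against.** **The primary algorithm is not a history-based classifier.** This stands. The severity model uses mainly blood markers and HRV, so label leakage does not apply to it as described. Only the treatment-effect route does. Leakage concerns the additional diagnostic classifier.

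**Medication is named as a confounder, and validation leaves sites out.** This stands in part. Adjustment would address some drug effects on the markers. It does not cover psychotherapy or prior diagnosis, and it gives no performance figure in unrecognised cases. Leave-site-out validation tests transfer between sites. If recognised cases occur at every site, the shortcut transfers too.

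**The full protocol or SAP may hold the predictor list and a subgroup analysis.** It may, and their absence from an article would not by itself be a finding. What the article does fix is the combination of mixed case sources, comparators without psychiatric disorder, a broad input statement and a purpose built on missed depression.

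**Unrecognised cases can enter, and the stated goal is broader.** Both are true. Study staff check eligibility directly, and a GP's part in that check does not mean the GP had recognised depression. Table 1 speaks of facilitating diagnosis generally, and the Discussion says a follow-up validation study is needed. Neither makes this study's pooled accuracy interpretable for missed cases.

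**Stronger readings that the text does not support.** A reader might infer that few missed patients are treated, but the Discussion's remark about treatment refers to detected patients. By the same remark, recognised does not mean treated. A reader might also infer a minimum clinic share by subtracting the 50 healthy controls from the 95. The article does not say that the rest are clinic cases, so only the ceiling holds.

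**Conclusion.** The point holds for the diagnostic classifier, and for the primary severity algorithm through treatment effects alone. As described, the plan allows accuracy to come partly from signs of recognition or treatment, and it provides no estimate in the unrecognised patients who motivate the tool. The size is unknown because the recognised or treated share is not given. The one bound available is that at most 95 participants come from outside GP offices. The document supports saying that the algorithm could learn these signs. It does not support saying that it will, or that sensitivity will be overstated by any particular amount.

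**What to change.** 1. State that psychiatric history and psychotropic medication are not inputs to the diagnostic classifier.
2. From the history and medication data taken at inclusion, code each case as previously diagnosed/treated or not.
3. Pre-specify sensitivity, estimated in held-out sites, in cases neither previously diagnosed nor treated, against non-depressed GP patients. Report it beside the pooled figure, and rest any claim about finding missed depression on it.

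**Cost.** Analysis wording and one derived variable. Status would rest on self-report unless GP records are available. The article lists neither record extraction nor psychotherapy status as collected, and 230 participants were already enrolled at 1 September 2023.

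The interval also widens. The worst-case 95% half-width, at 50% sensitivity, is 98/√n points: 4.5 with all 475 cases, 6.7 with 214, 9.0 with 119 and 14.1 with 48. The figure will probably be less favourable than the pooled one.
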